### Objectives

The primary objective of the Sparky Samba trial is to determine the feasibility of conducting a full-scale effectiveness RCT of the Sparky Samba intervention. The secondary objective is to explore the effect of Sparky Samba on functional and well-being measures, compared with activities as usual, in PwP.

### Recruitment and consent

Potential participants will be identified through specialist secondary care provisions (including both movement disorder and care of the elderly clinics) by clinical staff (doctors, nurses and PD specialist nurses). The trial will also be advertised on social media networks and through Parkinson’s UK Cymru, permitting participants to self-refer directly to the trial team. A screening log will be kept at each site and with the central trial team for analysis of feasibility measures pertaining to recruitment.

Participants are eligible for the trial if they meet all of the following inclusion criteria and none of the exclusion criteria, which have been defined to enable broad inclusivity of PwP. The inclusion criteria are: (i) anyone diagnosed with PD, (ii) aged 18 or older and (iii) able to provide informed consent. The sole exclusion criterion is previous and/or present participation (self-reported) in a Sparky Samba group (this does not exclude people with prior experience of music or dance).

Interested participants will be provided with a detailed information sheet providing information on the trial and what participation entails. Following confirmation of eligibility (either by clinician or self-report), participants will be registered on the trial database, constructed in Research Electronic Data Capture (REDCap),^19
20^ where they are automatically assigned a unique identification number. This number is used to label all study data to ensure participant confidentiality. Registration requires the provision of contact details to enable distribution of online patient-reported outcome measures, and consent is explicitly sought for the storage of this data. Access to contact details is restricted to the central trial team via password access to REDCap. Once registration is complete, participants are then asked to complete the online consent form in REDCap. Participants may also choose to complete the consent form on paper. If this option is chosen, completed consent forms will be stored at the research site.

Participants may withdraw their consent to participate at any time without their rights or clinical care being affected. Within the initial study information, it is made clear to participants that they can withdraw from all or specific parts of the trial (intervention, follow-up questionnaires, etc.) and that at the point a decision to withdraw is made, de-identified data collected about them will be retained for analysis.

### Randomisation

Participants will be randomised to the intervention or activities as usual in a 1:1 ratio, stratified by disease burden using the Hoehn and Yahr score of disease stage.^21^ The randomisation sequence, generated by the non-blinded, senior trial statistician, using nQuery software and stored securely so those enrolling participants cannot access it, will use permuted blocks of randomly varying sizes. The randomisation will be implemented via REDCap, and allocation to groups will be performed by the central trial team. Allocation will be communicated directly to the participant with concurrent notification to the recruiting site and, if required, the relevant local Sparky Samba group. Randomisation should occur within 14 days of the baseline assessment.

Owing to the nature of the intervention, this is a non-blinded trial. However, the trial statistician will remain blind to allocation until analysis is complete. Further, the Unified Parkinson’s Disease Rating Scale Part III^22^ will be video recorded, and ratings will be performed by a trained clinician blind to the allocation of the participant.

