Secondary outcomes to be collected include those measuring motor function, cognition, well-being, participation and self-efficacy. Individual outcomes are detailed in table 2. Functional outcomes are assessed within the hospital setting at baseline and again at 12 weeks following the intervention delivery period (table 3). Site staff delegated to perform the functional assessments will receive training from the central trial team at the site initiation visit, with an accompanying assessment manual and ad-hoc support from the trial team and clinically qualified members of the TMG. Demographic data (age, sex, ethnicity and educational level) and current medications will also be collected at baseline to provide cohort descriptives. Intervention adherence will be recorded weekly through self-report by the participant and by report from the Sparky Samba group leader/local organiser. At the end of the 12-week trial period, participants in the control group will be asked to detail the activities they have participated in for the previous 12 weeks. As retention is part of the feasibility outcome and the follow-up period is just 12 weeks long, we will not be enacting any specific strategies to boost retention beyond supporting travel to intervention sessions and enabling the flexibility described for completing outcome assessments.

**Table 2 T2:** Secondary outcomes collected in the Sparky Samba trial

Construct	Measure
Motor	Unified Parkinson’s Disease Rating Scale (UPDRS) section III(^22^): we will use this to assess global motor function in participants.
	Freezing of Gait (FoG)(^28^): this is a patient self-report measure designed to assess the severity of gait freezing in PwP.
	Dresden Falls Questionnaire (DREFAQ)(^29^): this is a patient self-report questionnaire designed to assess the risk and severity of falls, a common symptom in PwP.
	Mini-Balance Evaluation Systems Test (Mini-BES Test)(^30^): in this assessment participants are assessed across dynamic balance, functional ability and gait.
	Physical Activity Scale for the Elderly (PASE) (^31^): this questionnaire is designed to capture the level of physical activity across a range of usual activities over the past 7 days.
Cognition	Montreal Cognitive Assessment (MoCA)(^32^): we will use the truncated on-line version of the MoCA, known as XpressO, to assess cognitive function in participants. This is well validated for assessing cognitive function in PwP.

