### Data collection and management

Study data will be collected and managed using REDCap electronic data capture tools hosted at Cardiff University.^19
20^ REDCap is a secure, web-based software platform designed to support data capture for research studies, providing (1) an intuitive interface for validated data capture, (2) audit trails for tracking data manipulation and export procedures, (3) automated export procedures for seamless data downloads to common statistical packages and (4) procedures for data integration and interoperability with external sources.

All trial data recorded in REDCap features in-built data validations and mandatory completion of specific variables to promote quality control and data completion. Outcome data will be collected through a combination of patient-reported outcome measures (PROMs) completed directly within the database and in-person assessments conducted by research staff at the site (table 3). Following the provision of informed consent and confirmation of a baseline appointment from trial staff at the recruitment site, participants will be emailed a link to complete the PROMs ahead of their baseline assessment. If a participant chooses, they can complete the PROMs on paper copies at their baseline appointment. If a participant attends their baseline or follow-up appointment without having previously completed the PROMs in REDCap, they will be supported to do so either face to face at the appointment or by telephone by a member of the trial team.

Intervention adherence data will be collected directly from participants via REDCap. Participants will be emailed a brief attendance checklist weekly for up to a period of 14 weeks from the point of randomisation. Samba group leaders and group coordinators (local volunteers) will be asked to provide data on attendance on a pre-populated register provided to them by the central trial team.

Similarly, process evaluation questionnaires will be distributed through REDCap for remote completion. Process evaluation interviews will be conducted remotely using secure video conferencing software. Interviews will be audio recorded for verbatim transcription. Audio recordings will be deleted once transcripts have been cleaned, de-identified and incongruences verified. De-identified transcripts will be stored on a restricted access computer drive at Cardiff University.

All data management processes for the trial are contained in the Sparky Samba Data Management Plan.

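### The recruiting site is told each allocation while its own staff perform the 12-week Mini-BES Test, and nothing keeps that assessor unaware of the arm

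*Protocol article*

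**What the plan says.** All references are to the protocol article.

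- **Randomisation.** The central trial team performs the allocation. Then: "Allocation will be communicated directly to the participant with concurrent notification to the recruiting site", and the local Samba group is told if required. The section continues: "Owing to the nature of the intervention, this is a non-blinded trial". It then makes two exceptions. The trial statistician stays blind until analysis is complete, and UPDRS III is recorded on video, where "ratings will be performed by a trained clinician blind to the allocation of the participant".
- **Outcomes, text.** "Site staff delegated to perform the functional assessments will receive training from the central trial team at the site initiation visit". The functional outcomes are measured in hospital, at baseline and at 12 weeks.
- **Outcomes, Table 2.** The Mini-BES Test is listed under motor outcomes: "in this assessment participants are assessed across dynamic balance, functional ability and gait".
- **Table 3.** UPDRS, the Mini-BES Test and the MoCA (XpressO) are the outcome measures in the hospital columns. Randomisation comes after the baseline hospital visit. Adverse events are also assessed at the follow-up hospital visit.
- **Data collection and management.** In-person assessments are done by research staff at the site.
- **Analysis.** Secondary outcomes are summarised by arm, with 95% CIs for change from baseline. These are meant to supply effect size and variability for the power calculation of a future large trial.

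**The concern.** An observer scores the Mini-BES Test, so the score can be influenced by what that observer expects. It covers balance and gait, which are close to the benefit hoped for from a rhythm-based activity. The intervention explains why participants and group leaders cannot be masked. It does not explain why the site whose staff score the test should be told the arm. The plan already treats rater knowledge as a problem for one motor score taken at the visit and leaves the other open.

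What is at stake is the usefulness of the Mini-BES change as an input to planning the full trial. There is also a lost opportunity: a feasibility trial could learn whether site assessors can be kept unaware of allocation, and as written this one will not.

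**Working it through.** The plan gives no figure on this point, so the check is mainly a reading of the sections side by side.

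**Step 1. Which outcomes are exposed?**

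| Measure | Where taken at follow-up | How obtained | Protection from knowledge of allocation |
|---|---|---|---|
| UPDRS III | Hospital | Rated from video | Blinded clinician |
| Mini-BES Test | Hospital | Performed by site research staff | None described |
| MoCA (XpressO) | Hospital | Online test, cognitive | Not a motor outcome |
| FoG, DREFAQ, PASE | Home | Participant questionnaires | Participants know their arm; cannot be masked |

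The Mini-BES Test is the one hospital motor outcome without blinded rating.

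**Step 2. When can knowledge enter?** Table 3 puts the baseline Mini-BES Test on day 0 and randomisation afterwards, within 14 days. The baseline score therefore precedes allocation and only the 12-week score is exposed. Any shift at 12 weeks passes in full into the change from baseline.

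**Step 3. Does the assessor need the allocation?** Three site-related tasks after randomisation were checked.

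- Attendance comes from participants through REDCap and from group registers, not from the site.
- Control-arm activities are reported by participants.
- Serious adverse events are self-reported to the recruiting site, which might then need the arm. The central team holds it and can supply it.

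None of these requires the person scoring the Mini-BES Test to know the arm beforehand.

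**Step 4. What could it do to planning?** The article gives no SD, effect or bias for the Mini-BES Test. What follows is an illustration on assumed values. It also assumes that the full trial would be powered on this measure, which the article does not say.

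Per-arm size for 90% power at two-sided 5%, with effect d in SD units, is n = 2 × (1.960 + 1.282)² / d² = 21.0 / d².

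- Assumed true effect 0.4 SD: n = 21.0 / 0.16, giving 132 per arm.
- Same effect with an assumed 0.2 SD added by the assessor, so 0.6 SD: n = 21.0 / 0.36, giving 59 per arm.
- Real power with 59 per arm at 0.4 SD: Φ(0.4 × √(59/2) − 1.960) = Φ(0.213), about 58%.

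Over true effects of 0.3 to 0.5 SD and added shifts of 0.1 to 0.3 SD, real power runs from about 37% to 78% instead of 90%.

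This trial could not reveal such a shift. With 30 per arm, the half-width of a 95% CI for a between-arm difference would be 1.96 × √(2/30) = 0.51 SD. That interval serves only to show scale, since the Analysis section states CIs for change and no between-arm interval.

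**The case against.** The strongest reply is that the trial is openly non-blinded, claims no masking for the Mini-BES Test and so contradicts nothing. That is true, but it does not settle the matter. The stated reason for being non-blinded is the intervention, and the article itself masks the UPDRS III rater despite it. The notification is also a stated step, not a detail that the article merely leaves out.

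A second reply is that the article notifies the site, not the assessor. A reader might infer that the person who scores the test personally receives the allocation. The text does not say so, and recipient lists or delegation rules may be in the full protocol or the assessment manual. This limits the point to an absence of any stated separation.

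Third, masking would be imperfect. Adverse events, including falls, are asked about at the same visit, and participants who arrive with questionnaires outstanding are helped to complete them in person or by telephone. Disclosure is likely for some. This stands: the risk can be reduced, not removed.

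Fourth, the site has a safety role and may need the arm. This also stands, and the remedy has to allow for it.

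Finally, the Mini-BES Test is one of nine measures in Table 2, it is in none of the progression criteria, and the trial is not powered for clinical outcomes. That holds the point at a minor level.

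**Conclusion.** The point holds as a minor, inexpensive improvement. The site is told the allocation, its research staff perform the Mini-BES Test at 12 weeks, and no separation between the two is described, whereas UPDRS III is rated blind.

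The consequence is a risk of bias of unknown size and not a demonstrated bias. A reader might conclude that the Mini-BES change will be inflated in favour of the intervention. The direction is plausible, but nothing in the article establishes it or its size, and the power figures above only follow from the assumed shifts. Nor is the progression decision in doubt: recruitment, retention, adherence and data completeness do not depend on the Mini-BES score. What could be affected is one exploratory estimate and any sample size later built on it.

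**What to change.** Amend the Randomisation section so that allocation goes to the participant and, for the intervention arm, to the Samba group, and so that any notice to the recruiting site either

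- goes only to a contact who does not score the 12-week Mini-BES Test, or
- is held until that score has been entered in REDCap.

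The second option suits a site with too few staff to separate the roles; the article does not give site staffing. State that the central team will supply the allocation if the site needs it for a safety report. The Ethics and dissemination section mentions a sheet with local group details for intervention participants; if a site hands it over, someone other than the assessor should do so.

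Add to the assessment manual for the 12-week hospital visit:

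1. Score the Mini-BES Test before the adverse-event questions and before helping with any outstanding questionnaires.
2. Ask participants beforehand not to mention their group until the test is done.
3. Have the assessor record whether the allocation became known, and how.

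The cost is a change to notification recipients or timing, one extra data item and a few lines in an existing manual. The holding option needs no added staff or visits. The downside is that masking stays partial, because some participants will disclose; the record in item 3 shows how often and is itself useful feasibility information for the full trial. If the sponsor prefers to leave the notification as it is, the unmasked Mini-BES scoring should be named as a limitation wherever its estimate is used for planning.

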### Intervention

Sparky Samba is a samba band-based rhythm/drumming intervention delivered within the community for PwP. The setting is determined by the local availability of facilities, which are chosen by Sparky Samba leaders based on their geographic location and accessibility for group members. The group is facilitated by either a local samba musician or a regular member of the group who has been trained by the musician to deliver Sparky Samba sessions. The group size is usually around 8–15 participants but there is no minimum or maximum number required for any given session. While the sessions are designed specifically for PwP, supporters of PwP or partners of PwP are welcome to engage in the group sessions if they so wish.

In their first session, participants will be offered a choice of instrument that is suitable for their range of motion. This could range across tamborims, Snare drums (Caixa), Agogo bells, Surdos, Ganzá/Chocalho (shakers), Cuíca, Timbal, Pandeiro and the Repinique (figure 1). The Repinique, Timbal and Surdo drums are usually played in a standing position, whereas the Tamborim, smaller Surdo drums, Caixa, Agogo bells, Ganzá/Chocalho and Pandeiro can be played in a seated position. The Repinique is carried by the player using a strap over the shoulder which suspends the drum just below the drummer’s waist. Most instruments require at least one stick to play except the Ganzá/Chocalho or Pandeiro, which require movement of only one upper limb to play. During each session, participants will be instructed to follow a rhythmic sequence, as guided by the facilitator. Typically, the room is arranged with participants in a semi-circle, grouped by instrument type, facing the facilitator. Each rhythm is broken down into smaller sections with sub-groups (grouped by instrument) concentrating on their own section before coming together. The band leader/facilitator often carries a Repinique, as well as using Apitos (whistle) to signal breaks to participants. Each session lasts for approximately 60 min with time on either side of the session for the set-up and breakdown of instruments and seating.

**Figure 1 F1:**
[figure not shown]
Representative images of the range of instruments that may be used in a Sparky Samba session. A – Tamborim, B - Caixa, C – Agogo bells, D – Surdos, E – Ganzá, F - Timbal, G – Pandeiro and H - Repinique.

Work aligned to this trial has involved determination of the key factors constituting Sparky Samba as a health intervention which will be published elsewhere (manuscript under review).

Participants will be asked to attend as many sessions as possible, ideally weekly over a period of 12 weeks following randomisation. The Public and Patient Involvement (PPI) group stressed the importance of providing adequate notice to participants prior to starting the intervention, as individuals may need time to make necessary arrangements. Therefore, participants are given a 2-week grace period following randomisation to complete their first intervention session. Participants will be asked to attend at least six consecutive sessions and a minimum of 8 in total (completion of eight sessions in total will be regarded as adherent to the intervention). Adherence will be recorded by both self-report questionnaires and attendance registers from the Sparky Samba groups. The costs of participant travel to attend Sparky Samba sessions will be reimbursed. Alternatively, travel arrangements will be made upfront on behalf of the participants if they prefer. Following completion of the 12-week intervention period, participants can continue to attend the Sparky Samba group.

### Activities as usual

Participants randomised to the activities as usual control group will be asked to continue with their normal activities and attend any social or support groups they would ordinarily participate in over the 12 weeks. Participation in the trial does not necessitate prior or ongoing attendance at a particular social or support group. A physiotherapy or physical activity control group was considered to control for the type of movement included in a Sparky Samba session. However, this was discounted because while there is good evidence that physiotherapy and exercise can benefit PwP,^23
24^ the delivery of physiotherapy and exercise to this patient group, either through healthcare systems or community groups, is inconsistent across the region. Further, in conjunction with our PPI group, we were conscious that the opportunity for social interaction was a key aspect of attending Sparky Samba, which would not be achieved through attendance at healthcare-delivered physiotherapy sessions. The PPI group also suggested that many PwP are involved in other local community groups; therefore, activities as usual was chosen as the control. From the input of the PPI group, we anticipate that activities as usual may consist of activities such as walking, the gym, seated bowls or less physically orientated activities such as a Parkinson’s choir. Given the varied availability of specific Parkinson’s groups or organised community groups, we have not specified activities as usual but will be asking people randomised to this group to specify the activities they have taken part in over the 12-week trial period. This will help us determine the feasibility of using ‘activities as usual’ as a comparator condition in a future effectiveness trial of Sparky Samba. Following completion of the 12-week follow-up assessment, participants randomised to activities as usual will be offered the opportunity to join their local Sparky Samba group. As for trial participants initially randomised to the intervention group, any costs associated with attendance at the Sparky Samba group will be supported by the trial for a period of 12 weeks.

During the intervention delivery period, there are no restrictions imposed on any additional treatment participants may require for their PD or otherwise. If changes in health status and/or treatment affect their participation in the trial, this will be recorded via notification of withdrawal.

### Outcomes

The primary outcome for this trial is feasibility as defined by participant recruitment, retention, intervention adherence and data completeness according to pre-specified criteria. Thresholds for the feasibility criteria are detailed in table 1.

**Table 1 T1:** Measures of feasibility and pre-defined criteria for success used to determine the primary outcome

Variable	Progression criteria		
	Red	Amber	Green
Recruitment			
% of people approached who are willing to participate (100*(number consented/number approached)%)	<5%	5–19.9%	≥20%
Number recruited	<25	25-44	45-60
Retention			
% of participants attending the primary 12-week endpoint assessment (100*(number attending/number consented)%)	<50%	50–89.9%	≥90%
Adherence			
% of participants adherent to the intervention (attending ≥8 sessions) (100*(number adherent/number consented)%)	<50%	50–79.9%	≥80%
Data completeness			
% of participants completing at least 90% of baseline measures (100*(number completing ≥90%/number consented)%)	<70%	70–94.9%	≥95%
% of participants completing at least 90% of follow-up measures (100*(number completing ≥90%/number consented)%)	<50%	50–74.9%	≥75%

Secondary outcomes to be collected include those measuring motor function, cognition, well-being, participation and self-efficacy. Individual outcomes are detailed in table 2. Functional outcomes are assessed within the hospital setting at baseline and again at 12 weeks following the intervention delivery period (table 3). Site staff delegated to perform the functional assessments will receive training from the central trial team at the site initiation visit, with an accompanying assessment manual and ad-hoc support from the trial team and clinically qualified members of the TMG. Demographic data (age, sex, ethnicity and educational level) and current medications will also be collected at baseline to provide cohort descriptives. Intervention adherence will be recorded weekly through self-report by the participant and by report from the Sparky Samba group leader/local organiser. At the end of the 12-week trial period, participants in the control group will be asked to detail the activities they have participated in for the previous 12 weeks. As retention is part of the feasibility outcome and the follow-up period is just 12 weeks long, we will not be enacting any specific strategies to boost retention beyond supporting travel to intervention sessions and enabling the flexibility described for completing outcome assessments.

**Table 2 T2:** Secondary outcomes collected in the Sparky Samba trial

Construct	Measure
Motor	Unified Parkinson’s Disease Rating Scale (UPDRS) section III(^22^): we will use this to assess global motor function in participants.
	Freezing of Gait (FoG)(^28^): this is a patient self-report measure designed to assess the severity of gait freezing in PwP.
	Dresden Falls Questionnaire (DREFAQ)(^29^): this is a patient self-report questionnaire designed to assess the risk and severity of falls, a common symptom in PwP.
	Mini-Balance Evaluation Systems Test (Mini-BES Test)(^30^): in this assessment participants are assessed across dynamic balance, functional ability and gait.
	Physical Activity Scale for the Elderly (PASE) (^31^): this questionnaire is designed to capture the level of physical activity across a range of usual activities over the past 7 days.
Cognition	Montreal Cognitive Assessment (MoCA)(^32^): we will use the truncated on-line version of the MoCA, known as XpressO, to assess cognitive function in participants. This is well validated for assessing cognitive function in PwP.
Quality of Life	Parkinson’s Disease Questionnaire (eight items) (PDQ-8)(^33^): this is a self-completion participant-reported outcome designed to address aspects of functioning and well-being for those affected by PD. The PDQ-8 asks one question from each of the domains of the longer PDQ-39; activities of daily living, mobility, emotional well-being, stigma, social support, cognition, communication, bodily discomfort, with questions about thoughts of death and self-harm being removed.
Self-Efficacy	Oxford Participation and Activities Questionnaire (OxPAQ)(^34^): this is a validated self-report questionnaire designed to assess the degree of activity and participation of those with chronic conditions taking part in community-based interventions.
	Lorig Self-Efficacy Scale(^35 36^): this scale will be used to measure self-efficacy related to exercise (exercise sub-scale only).

PD, Parkinson’s disease; PwP, people with PD.

**Table 3 T3:** Participant timeline for completion of trial assessments and intervention delivery

Procedures	Visits					
	Baseline visit (week 0)			Intervention delivery (days 0–84+14 days)	Follow-up visit (week 12±5 days)	
	At home (days −3±2 days)	At hospital (day 0)	Remote (days 0+14 days)		At home (days 85±5 days)	At hospital (days 88±2 days)
Informed consent	x					
Demographics	x					
Medications		x				
Hoehn and Yahr staging		x				
Randomisation			x			
Intervention delivery				x		
Intervention adherence				x	x	
UPDRS		x				x
FoG	x				x	
Mini-BES Test		x				x
DREFAQ	x				x	
MoCA (XpressO)		x				x
PDQ-8	x				x	
OxPAQ	x				x	
Lorig	x				x	
PASE	x				x	
Adverse event assessments				x	x	x
Process evaluation questionnaire					x	

DREFAQ, Dresden Falls Questionnaire; FoG, Freezing of Gait; Mini-BES Test, Mini-Balance Evaluation Systems Test; MoCA, Montreal Cognitive Assessment; OxPAQ, Oxford Participation and Activities Questionnaire; PASE, Physical Activity Scale for the Elderly; PDQ-8, Parkinson’s Disease Questionnaire (eight items); UPDRS, Unified Parkinson’s Disease Rating Scale.

